**e. Data management**

Using standard protocols for the questionnaire, measures and data coding, polyclinic pediatricians will be responsible for data collection. We have established a robust data management system and will build on the expertise gained in earlier follow-ups of the trial. There will be a peripherally located Microsoft Access database at the Data Center in Minsk for administration of follow-up invitation letters, appointment information, and monitoring conformity with other study procedures.

Data flow will be as follows. Copies of data forms containing the results of the physical examination and the questionnaires will be transported by driver from each polyclinic on a monthly basis to the Data Center in Minsk. Carbon copies of the forms will be kept at the polyclinic in case of loss in transit. Data will be entered into a Microsoft Access database, with built in logic checks, by trained data entry staff. Spirometric and cognitive data will be downloaded onto encrypted USB sticks, transported to Minsk by the driver and automatically uploaded into the database to prevent transcription errors. On a weekly basis, the Minsk-based data coordinator will run a program to identify logical errors and missing values, with corrections/completions requested by telephone and/or mail. Each month, a copy of the database will be e-mailed to the master database in Bristol, and subsequently to the analyst in Boston, who will perform ongoing analyses of data quality (blind to trial arm). She will calculate intra-class correlations to evaluate clustering, and will feed results back to the pediatricians at workshops held every 6 months.

**f. Organization of study operations**

Study operations will mirror the procedures we have successfully applied to PROBIT III, and are detailed more fully in the **Multiple PI Leadership Plan**. Drs. [name] and [name] together will be responsible for the scientific direction and overall conduct of the project. [name] will work with the UK-based Research Coordinator ([name]) to oversee day-to-day study logistics, including importation of equipment, planning workshops, developing training materials, creation and maintenance of the study databases. [name] will communicate with the Minsk-based co-ordination center and data entry team. [name] will supervise the US-based Project Manager ([name]) to plan and oversee the data monitoring and data auditing visits. [name] is also an experienced statistical analyst. She will receive monthly data downloads from Minsk, which she will use to create data summaries and identify missing, implausible, or outlying values, and will communicate these potential data errors back to the data entry team in Minsk. She will be the lead analyst for all analyses of the PROBIT age 15-16 year outcome data. With [name] supervision, [name] will handle all communications with the Harvard Pilgrim Health Care IRB, and will track all expenses on the project.

Drs. [name] and [name] will communicate regularly with the study leadership in Minsk, including [name], Director of the Belarusian Maternal and Child Health Center and Scientific Director for PROBIT in Minsk, and [name], Director of Epidemiologic Studies at the Maternal and Child Health Center and Study Coordinator for PROBIT. To minimize any potential for confusion or miscommunication, [name] will be responsible for communicating via email with [name] and [name], with the help of an experienced Russian-English interpreter as has been done to date. At each twice-yearly visit to Minsk, the entire study leadership team (Drs. [name], [name], [name], [name], and [name]) will meet as a group to discuss operational issues.

**2.3.5. Analysis Plan**

**a. Overall Analytic Plan**

Prior to formal analysis, we will construct tables, histograms, and box-and-whisker plots of the collected data to search for missing data and implausible or extreme values that may suggest error in measurement, recording or data entry. Where possible we will return to paper records to find missing data and determine if errors can be corrected. Histograms of residuals will be investigated for normality and outcomes transformed when necessary to satisfy normality and other model assumptions, e.g., constant variance or linearity of effect. Because this is a randomized trial, the primary approach will be an intention-to-treat (ITT). All analyses will allow for the clustered nature of the data.

**b. Exposure, outcomes, and covariates**

The exposure will be randomization to the breastfeeding promotion intervention or to the control group. The expected sample size is 14,000 children from 31 polyclinics.

The main neurocognitive outcomes will be the *Mindstream* scores standardized to an IQ scale (mean 100, SD 15) for memory; executive function; visual-spatial accuracy; verbal function; attention; information processing; motor skills; and a global cognitive score. Vision will be assessed using LogMAR acuity, analyzed as a continuous variable (given its more normal distribution compared to Snellen acuity measures); prevalence of reduced LogMAR visual acuity will also be considered between intervention groups. Atopic eczema outcomes will be evidence of flexural dermatitis around the eyes, the back of the neck, front of the elbows, back of the knees, or ankles, as identified by a trained PROBIT pediatrician; secondary atopic eczema outcomes will include responses to the skin questions from the ISAAC questionnaire. Respiratory function outcomes will be PEFR, FEV_1_ and FVC, each expressed as internal z-scores adjusted for height, age and sex. Adiposity outcomes will be body mass (BMI), fat mass (FMI), and fat-free mass (FFMI) indices, waist-to-height ratio and overweight as BMI between the 85th to <95th percentiles and obesity as BMI at or above the 95th percentile, based on the Centers for Disease Control and Prevention (CDC) 2000 age- and sex-specific reference data. Blood pressure outcomes as continuous measures of systolic and diastolic blood pressure.

Since the number of polyclinics randomized in PROBIT (31) was relatively small, imbalances in baseline covariates sufficient to confound the effect estimates may have occurred. We will therefore conduct a secondary analysis in which we control for any predictors of our outcomes (unadjusted P<0.1) that are also found to be associated (P<0.1) with randomization status. To date, PROBIT analyses suggest that this circumstance is unlikely to occur (see **Table 1**); no evidence of confounding by individual-level covariates was evident in PROBIT I, II or III.^17,21^ The main hospital-level potential confounders are geographic region and urban versus rural location.

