The **specific aims** of the current proposal are to perform an intention-to-treat analysis comparing the randomized intervention *vs.* control arm. We will estimate the unconfounded, causal effects of breastfeeding promotion for the following hypotheses:

1. Prolonged, exclusive breastfeeding improves neurocognitive outcomes, including verbal and non-verbal cognitive ability and vision at age 15-16 years.
2. Prolonged, exclusive breastfeeding improves spirometric lung function and reduces rates of atopic eczema at age 15-16 years.
3. Prolonged, exclusive breastfeeding reduces adiposity and blood pressure at age 15-16 years.

We will also use data already collected as part of the PROBIT study to perform observational analyses examining associations of early life exposures, including birth characteristics and infant growth and feeding, with child health outcomes at age 6.5, 11 and 15-16 years, including cognition, asthma, atopy, dental health, adiposity, blood pressure, bloodspot measures of cardiometabolic health, neurocognitive outcomes, and lung function.

Furthermore, we will analyze associations of treatment assignment and breastfeeding duration with maternal health and adiposity at 11 years postpartum, using data already collected as part of PROBIT III.

The proposed research will provide an estimate of the causal effect of breastfeeding on outcomes meaningful for health in childhood and throughout the lifecourse. Understanding the causal effects of breastfeeding is important to maximize the population-wide impact of guidelines focusing on early nutrition, by providing robust data, ensuring consistent conclusions, and minimizing potential harms. Although different in many socioeconomic, cultural, and economic respects from the United States, Belarus is a relatively developed country, with strict hygienic standards, high immunization rates, low incidence of infection, low rates of infant and child mortality, similar types of formula feeds and accessible health care services. The results of this current proposal are therefore likely to inform policy in the US and many other countries.

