**2. Research Strategy**

**2.1. Significance**

Breastfeeding is widely promoted as a cornerstone of public health.^1^ Observational studies, including several involving co-applicants on the current proposal, suggest that being breastfed reduces risks for obesity, hypertension, diabetes, heart disease, asthma and atopy. ^2-8^ Yet mothers who breastfeed differ from mothers who formula feed: they are wealthier, better educated, less likely to smoke, and more likely to engage in other beneficial health behaviors.^9,10^ Thus, residual or unmeasured confounding, rather than breastfeeding itself, may explain observed associations between breastfeeding and health outcomes. To disentangle the health effects of breastfeeding from the characteristics of mothers who choose to breastfeed, we will perform an intention-to-treat analysis of a breastfeeding promotion intervention on neurocognitive and lung function outcomes in a large, well-characterized population of children followed from birth. Each of the outcomes to be studied are known to be sensitive to early life exposures, which can permanently program organ structure and function resulting in profound influences on health, function, and mortality risks throughout the lifecourse. In the sections below, we summarize the current evidence for associations of breastfeeding with each of the primary outcomes of this proposal, and highlight areas needing further study.

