**b. New data**

As in PROBIT I-III, polyclinic pediatricians will locate and invite children to attend the follow up clinic examination where the pediatricians will collect the measures described below.

***Informed consent****.* As we have done at each stage of data collection, pediatricians will obtain verbal informed consent via telephone or written informed consent from a parent for each participating child. They will also obtain verbal assent from children. Belarusian law disallows minors from providing written informed consent.

***Neurocognitive function.***  Cognition will be assessed using the *Mindstreams* Global Assessment Battery (NeuroTrax Corp), a software package that is installed onto PCs and contains a validated computerized cognitive battery with multiple domains.^143-145^ After detailed review of available instruments, we chose *Mindstreams* because it tests a breadth of cognitive function; is brief (≈ 45 mins); includes a verbal domain (the domain most strongly associated with breastfeeding in PROBIT II); is self-administered; has an available, validated Russian language version; requires little computer literacy (only mouse clicks and number pad entries); and includes built-in trial tests with feedback before starting, to ensure comprehension. Other available tests are longer (> 1 hour); do not include verbal ability or have existing verbal tests that may not be generalizable to Russian; or are administered by trained personnel, so are not practical/cost-effective in our large trial. The *Mindstreams* non-verbal ability domain tests reaction time, immediate and delayed non-verbal memory (geometric figures), motor skills (e.g. hand-eye coordination; spatial recognition) and visual-spatial processing. The verbal ability domain tests immediate and delayed verbal memory (words; pictures) and word recognition. Aggregate outcome parameters will be computed from raw data using automatic algorithms, blind to intervention, standardized by age and fitted to an IQ-style scale (mean 100, SD 15). Standardized parameters that measure similar cognitive functions will be averaged to produce 7 ‘index scores’, each summarizing performance in a single domain:^146^ memory; executive function; visual-spatial perception; verbal function; attention; information processing; and motor skills. A global cognitive score, reflecting general cognitive status, will be computed as the average of the index scores.

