**c. Statistical Analysis.**

All analyses will allow appropriately for the clustering. We will use random effects models to account for correlation within polyclinic, as is recommended for cluster randomized trials. Results will be reported as mean differences. We will derive 95% confidence intervals and Wald tests of the null hypothesis of no association between intervention groups. Effect modification will be addressed by stratification and by formally testing for statistical interaction by introducing appropriate cross-product terms. We will initially examine results stratified by sex to ensure comparability, before we consider combining results for boys and girls.

It is well known that “per-protocol” analyses of randomized trials, in which participants are grouped according to the intervention they received, rather than that to which they were randomized, may be seriously biased. It is for this reason that the primary analyses for this study will be based on intention-to-treat. However, this approach may substantially underestimate the effect of the true exposure of interest (breastfeeding exclusivity and duration), since there was not complete contrast of breastfeeding status between the randomized groups: many intervention mothers did not exclusively breastfeed for 6 months, whereas some control mothers did. There is a substantial statistical literature showing that causal effects of interventions may be validly estimated from randomized trials, allowing appropriately for non-compliance with the intervention.^152-155^ Thus, in secondary analyses, we will apply instrumental variable methods to estimate the causal effect of the difference in breastfeeding exclusivity and duration achieved between the two randomized groups on our outcomes. In this approach, we will use randomization status as the ‘instrument’ that is independent of any confounders of the exposure-outcome relationship, and is related to the outcomes only via the exposure. We will thus validly estimate the unbiased effect of breastfeeding itself on cognition, vision, and lung function. Although these analyses will address the attenuation of the effect of breastfeeding that is inevitable in intention-to-treat analyses, they are unlikely to increase the power of the study, so sample size calculations are not affected.

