**2.3.6. Power**

Based on follow-up in PROBIT I-III, we expect 14,000 participants in PROBIT IV. We calculated detectable differences based on this number of subjects in 31 clusters, an intention-to-treat (ITT) analysis, 80% power, 5% significance, and used a realistic value (0.01) of the intra-cluster correlation coefficient (ICC) based on the ICCs of outcomes in PROBIT I-III. The effective sample size in PROBIT IV, allowing for the clustered design, is the total number of anticipated participants (14,000) divided by the design effect (*Deff*), where *Deff* = 1+(*n*-1)×ICC and *n* is the average number of individuals per cluster (n=14,000/31=451).^156^ Thus, the design effect for an ICC of 0.01 is 1+4.5=5.5 and the effective sample size is 2,500 children (14,000/5.5). Expected means and SDs for each outcome were taken from childhood cohorts of similar age. Mean detectable differences, assuming exposure groups are dichotomized at the midpoint, are calculated as the product of the SD of each variable and the standardized difference (i.e. 0.1 given an effective sample size of 2,500^157^). For the categorical atopic eczema outcome at the 16-year follow-up (flexural eczema on skin examination), the study has 94% power at the 5% significance level to detect a 50% reduction in atopic eczema prevalence between the two study groups, similar to PROBIT I.^21^

**Table 5** shows the mean differences that can be detected in the comparison of the two randomized arms by ITT and the corresponding effect due to breastfeeding that would have to be present to achieve those ITT differences. The breastfeeding effect is based on the difference in exclusive breastfeeding at 3 months of 43% in the intervention arm and 6% among controls, and is derived by dividing the ITT differences by 0.37=37% (the difference in exclusive breastfeeding in the 2 arms). For comparison, published differences are shown. The sample size is adequate for detecting important differences in the outcomes (**Table 5**). If we fail to find associations in the ITT analysis, the study is powered to have narrow confidence intervals (CIs) around null estimates. The 95% CIs for zero mean differences, assuming an effective sample size of 1250 in each arm ((14,000/Deff) ÷ 2) and means/SDs in Table 2, would be: cognitive score ± 1.2; FEV_1_ ± 40mls; FVC: ± 45mls; PEFR: ± 60mls/s.

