***Table 5:* *Expected control group means, SDs, and differences detectable (alpha= 0.05, 80% Power)***

| **Continuous Outcomes** | **Mean** | **SD** | **Mean detectable differences: ITT** | **Breastfeeding effect to produce detectable effect** | **Differences observed in other studies** |
| --- | --- | --- | --- | --- | --- |
| Global cognitive score | 100 | 15 | 1.5 | 4.1 | 2-5^16^ |
| FEV_1_ (mls)^a^ | 3345 | 480 | 48 | 130 | 40^59^ |
| FVC (mls)^a^ | 3700 | 575 | 58 | 150 | 54-103^58,59^ |
| PEFR (mls/s)^a^ | 6200 | 800 | 80 | 200 | 180^4,59^ |
| LogMar visual acuity | 0.02^b^ | 0.2^b^ | 0.02 | 0.05 | 0.05^5-7,101,158^ |
| Systolic blood pressure (mmHg)^159^ | 99.9 | 9.6 | 1.15 | 3.11 | Meta-analysis: 1.4 Max difference: 6.5^160^ |
| Diastolic blood pressure (mmHg)^159^ | 57.0 | 6.8 | 0.82 | 2.22 | Meta-analysis: 0.5; Max differences: 3.4^161,162^ |
| Body mass index (kg/m^2^) ^c^ | 16.2 | 2.0 | 0.024 | 0.06 | 0.4^163^; 0.28-0.57^72,164^ |

^a^Data from ALSPAC, standardized for height; ^b^Northern Ireland Childhood Errors of Refraction study (personal communication); ^c^Estimates of means and SDs obtained from ALSPAC.

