## Intervention

Experimental group: breastfeeding promotion intervention at maternity hospitals and affiliated polyclinics

Control group: continuation of maternity hospital and polyclinic practices existing at time of randomisation

Intervention type

Other

Phase

Not Applicable

Drug names Primary outcome measures

One or more episodes of gastrointestinal infection in first 12 months of life.

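### The protocol calls eight cognitive scores main and lists 14 further age-16 outcomes without rank, so no outcome is named as deciding any aim

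*Protocol*

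**What the plan says.** Section 2.3.5 b of the Protocol groups the Mindstreams results as the main neurocognitive outcomes: memory, then "executive function; visual-spatial accuracy; verbal function; attention; information processing; motor skills; and a global cognitive score". Section 2.3.4 b defines the global score as the average of the seven domain indices.

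Section 2.3.5 b then lists two vision outcomes, flexural eczema on examination, three lung measures, six adiposity outcomes and two blood pressures. Its only signs of rank are that the ISAAC skin questions are labelled secondary and that reduced acuity is worded as an addition to continuous acuity.

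On testing, section 2.3.5 c says: "We will derive 95% confidence intervals and Wald tests of the null hypothesis of no association between intervention groups". The power section assumes "an intention-to-treat (ITT) analysis, 80% power, 5% significance", and the heading of Table 5 repeats the level: "differences detectable (alpha= 0.05, 80% Power".

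Three places bear on what is primary:

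- Section 2.1 says "we summarize the current evidence for associations of breastfeeding with each of the primary outcomes of this proposal". The subsections that follow identify broad domains, not single outcomes.
- The ISRCTN record reproduced in the Protocol gives the trial's primary outcome as "One or more episodes of gastrointestinal infection in first 12 months of life". It lists the age-16 outcomes among the secondary ones, unranked.
- Aim 1 is worded as a claim: "Prolonged, exclusive breastfeeding improves neurocognitive outcomes, including verbal and non-verbal cognitive ability and vision at age 15-16 years".

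**The concern.** Aim 1 follows up a disputed finding. At 6.5 years verbal IQ differed by 7.5 points (95% CI 0.8 to 14.3), while performance IQ (2.9; -3.3 to 9.1) and full-scale IQ (5.9; -1.0 to 12.8) did not reach significance. Section 2.1.1 concedes that chance or systematic overestimation could explain the verbal result. This phase is meant to help settle that.

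As written, any one of eight cognitive scores could be cited in support of Aim 1. The signals within the protocol also differ. Table 5 gives a detectable difference for the global score only. Section 2.3.4 b, in its reasons for choosing the instrument, says that it "includes a verbal domain (the domain most strongly associated with breastfeeding in PROBIT II" data. If verbal and global scores part company again, the protocol gives no rule for which one answers the question.

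**Working it through.** **Count of outcomes (section 2.3.5 b).** 8 cognitive + 2 vision + 1 eczema + 3 lung + 6 adiposity (BMI, FMI, FFMI, waist-to-height ratio, overweight, obesity) + 2 blood pressure = 22. The ISAAC items are not counted.

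**The plan's own figures.** Design effect = 1 + (451 - 1) × 0.01 = 5.5, and 14,000 / 5.5 = 2,545, stated as 2,500, or 1,250 per arm. The half-width of the null 95% interval for cognition is 1.96 × 15 × √(2/1,250) = 1.18, stated as 1.2. The interval therefore corresponds to a two-sided 5% test, which is used below. The stated detectable difference of 0.1 SD does not reproduce exactly: (1.960 + 0.842) × √(2/1,250) = 0.112 SD. That is a separate matter and does not affect this point. The protocol states no family-wise error rate.

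**Independent tests, no true effect.** The chance of at least one result at 5% is 1 - 0.95^k.

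- k = 8: 1 - 0.95^8 = 33.7%. In the favourable direction only: 1 - 0.975^8 = 18.3%.
- k = 22: 1 - 0.95^22 = 67.6%.

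**Correlated tests.** The protocol gives no correlations between outcomes, so a range is assumed. The test statistics were simulated as multivariate normal (400,000 draws), with the global score as the standardised mean of the seven indices, a common correlation within each domain and none between domains.

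| Within-domain correlation | Eight cognitive, any | Eight cognitive, favourable only | All 22, any |
|---|---|---|---|
| 0.1 | 31% | 16% | 66% |
| 0.3 | 27% | 14% | 63% |
| 0.5 | 23% | 12% | 58% |
| 0.7 | 18% | 9% | 51% |
| 0.8 | 15% | 7% | 46% |
| 0.9 | 11% | 6% | 41% |

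With 0.2 between domains as well, the all-22 figure at 0.5 becomes 55%. If all 22 outcomes correlate at 0.5, it is 44%.

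Taken aim by aim, over correlations 0.9 to 0.1, the chances are 18% to 37% for Aim 1 (cognition and vision), 13% to 19% for Aim 2 and 17% to 33% for Aim 3.

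**Verbal against global.** Suppose only verbal function shifts, by the 2.80 standard errors that its own test detects with 80% power. The mean of seven statistics then shifts by 2.80 / 7 = 0.40, with standard deviation √((1 + 6r)/7) at correlation r.

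- r = 0.3: SD 0.632, standardised shift 0.63, chance of exceeding 1.96 = 9.2%.
- r = 0.5: SD 0.756, shift 0.53, chance 7.6%.
- r = 0.7: SD 0.862, shift 0.46, chance 6.7%.
- r = 0.9: SD 0.956, shift 0.42, chance 6.2%.

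Below r = 0.3 the chance is higher: 13% at 0.1 and 18% at 0.

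**Cost of sharing 5% between two outcomes.** At a first step of 2.5%, (2.241 + 0.842) / (1.960 + 0.842) = 3.08 / 2.80 = 1.10.

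**The case against.** Multiplicity procedures are commonly left to the statistical analysis plan, which is not at hand, and the 5% in the power section is a sizing input, not a decision rule. That stands: the absence of an alpha split or gatekeeping scheme is not a finding here. What remains is that the protocol has its own analysis section, speaks of primary outcomes, and fills that place with an unranked list. Choosing the deciding outcome is a protocol decision.

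A reader might infer that a false positive somewhere is more likely than not. The documents do not support that as a flat statement. It concerns all 22 outcomes pooled, although the aims are three separate questions. It fails once within-domain correlation exceeds about 0.7, and no correlations are given. Overlap is partly built in: the global score averages the other seven, and overweight and obesity are cut-points of BMI. Only favourable results could support the aims as worded, which roughly halves the cognitive figure. For the eight cognitive scores the chance is never above about one third.

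A reader might also infer that there is no ranking at all. That is too strong, given the ISAAC label, the wording on reduced acuity, and Table 5's choice of the global score. None of these names a deciding test.

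The verbal-only scenario is an assumption: at 6.5 years the performance and full-scale estimates were also positive. It shows that the two scores can disagree, not that they will. It is also fair that this is a late follow-up with a stress on estimation. The aims are nonetheless worded as hypotheses, and tests are planned.

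**Conclusion.** The point holds in this form: the protocol's own outcome section does not say which of eight main cognitive scores decides Aim 1, and ranks almost none of the other outcomes. Neither section 2.1 nor the registry text settles it.

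For cognition, the chance of at least one nominally significant score with no true effect is about 11% to 34%, against 5% for a single named test. A favourable one arises in about 6% to 18%. These figures rest on two-sided 5% tests and assumed correlations. The pooled figure for 22 outcomes is context only. The practical weakness is the missing rule for when verbal and global results differ, as verbal and full-scale results did at 6.5 years. Confidence is high that the deciding outcome is not named. The exact error rate cannot be fixed from the documents.

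**What to change.** In section 2.3.5 b, before arm-level results are seen, name the deciding outcome or outcomes for each aim from those already listed. Label the rest secondary, reported with 95% intervals and no confirmatory claim.

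For Aim 1 the natural candidate is the global cognitive score, the only cognitive score in Table 5. If a second is wanted, verbal function is the result being followed up, and the two should share the 5% level. The sponsor should choose the outcomes for Aims 2 and 3 and the place of vision, since the protocol gives no basis for a reviewer to choose. Section 2.1's reference to primary outcomes should then match that list.

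The change needs wording only, with no new data or visits. With two outcomes sharing 5%, the detectable difference rises by about 10% at the first step, and an isolated result elsewhere can no longer be presented as confirming an aim. Timing matters: the registry printout bound into the Protocol was processed in February 2017, after the registered end date of 31 December 2015. The change should therefore be dated and should state that arm-level results had not been seen. If they have been seen, the ranking should be reported as post hoc.
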